### Primary outcome measure

#### VISA-A questionnaire

The VISA-A questionnaire has been shown to be a valid, reliable and easy-to-use outcome measure tool for intervention studies on AT [46]. It consists of eight questions regarding pain and function during both daily living and sporting activities. The overall score is between 0 and 100 where higher scores represent reduced pain and improved function. An improvement of 21 points between 2 and 12 weeks of a rehabilitation program have been typically observed [44]. While the VISA-A score will not determine eligibility for inclusion into the study, it will be used to map progress over the course of the rehabilitation program and in the follow-up period. The difference in VISA-A score between both training protocols from baseline testing to the outcome testing at 6 weeks, 12 weeks, 3, 6 and 12 months; will formulate the primary outcome measure for this study.

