### Randomisation and blinding

Participants will be assessed at baseline before being randomly assigned to the intervention group or control group and will follow a prescribed rehabilitation program for 12 weeks. See Table 3 for a summary of the study design. The randomisation will be performed using the online tool www.sealedenvelope.com and the participant will be handed an envelope from an independent observer not involved with the study, containing their respective group allocation number. The principal investigator and training group investigators will be blinded to the group randomisation process. These procedures have been used in similar studies [45]. The participants will be prescribed with an exercise program with video demonstrations of each exercise under the supervision of the investigator in their respective group. The program will be carried out at home or in a local gym in addition to supervised rehabilitation sessions every 2–3 weeks at SSC. Testing will take place again at week 6 and 12. Follow-up interviews will take place at 6, 12 and 24 months after baseline testing. The investigator involved with the testing and follow-up interviews will also be blinded to the group allocation. The primary outcome measure will be changes to the VISA-A questionnaire. Secondary outcome measures will include plantar flexor strength, lower limb reactive strength, biomechanics and running gait.

**Table 3 Tab3:** Overview of outcome measures over the course of the study

	Baseline	Week 6	Week 12	6 months	12 months	24 months
Body mass	X					
Body height	X					
Body mass index	X					
Sport/activity level	X			X	X	XX
VISA-A Questionnaire	X	X	X	X	X	X
Isokinetic plantar flexor peak torque (knee extension)	X	X	X			
Isokinetic plantar flexor peak torque (knee flexion)	X	X	X			
3D running gait analysis	X	X	X			
Double leg drop jump		X	X			
Single leg drop jump		X	X			
Single leg horizontal rebound		X	X			
Exercise compliance		X	X	X		

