### Statistical analysis and power calculation

This study is powered to detect a change of 15 points on the VISA-A questionnaire, similar to previous studies investigating clinical changes after a rehabilitation program [61, 62]. The average reported change in a VISA-A questionnaire after a 12-week intervention is 21 points with a standard deviation 6.6 points [44]. Assuming a power of 80% and a two-sided 5% significance level, a total of 25 participants in each group would be required. Allowing for a conservative drop-out rate of 15%, the proposed total sample size is 60, with 30 in each group. This number is similar to those used in other high quality injury rehabilitation RCT studies [40, 45].

Statistical analysis will be performed using R (R Studio version 1.2.5). Descriptive statistics will be used for all continuous variables, and means and standard deviations will be reported. Comparisons between both groups at different timepoints will be assessed using Student’s independent samples two-tailed t-tests. An intention to treat analysis will be used to test a within-group and between-group change in VISA-A questionnaire score at testing and follow-up timepoints, using a repeated measures Analysis of Covariance (ANCOVA). The primary outcome measure - changes to the VISA-A questionnaire, will the dependent variable, group will the between participants factor and time will be the covariate. Non-parametric equivalents (Matt-Whitney U-Test and Friedman Test respectively) will be used if a Shapiro-Wilk test indicates that the assumption of normality has not been met. A multiple regression analysis will be used to investigate the total variance and the relative weight of each independent variable with changes in VISA-A score as the dependent variable. The independent variables will be changes in plantar flexor strength, reactive strength and lower limb biomechanical variables, as well as exercise adherence and fidelity. Effect sizes will be reported using partial eta squared threshold values of > 0.2 (small), > 0.5 (moderate), and > 0.8 (large). Statistical significance will be accepted at α = 0.05.

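### The primary outcome covers four distinct visits (five listed, one a duplicate), and no visit or contrast is named to decide the trial at the 5% level

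*Protocol article*

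**What the plan says.** - **Primary outcome, general wording** (Randomisation and blinding): "The primary outcome measure will be changes to the VISA-A questionnaire". No time point is attached.
- **Primary outcome, detailed wording** (Primary outcome measure, VISA-A questionnaire): the between-protocol difference in score "from baseline testing to the outcome testing at 6 weeks, 12 weeks, 3, 6 and 12 months; will formulate the primary outcome measure".
- **Visit schedule** (Table 3): the columns are "Baseline Week 6 Week 12 6 months 12 months 24 months", and VISA-A is marked in every one. The text of the same section agrees: testing at weeks 6 and 12, then "Follow-up interviews will take place at 6, 12 and 24 months after baseline testing".
- **Analysis** (Statistical analysis and power calculation): "Comparisons between both groups at different timepoints will be assessed using" two-tailed independent-samples t-tests; this sentence names no outcome. The next sentence gives VISA-A an intention-to-treat repeated measures ANCOVA for change within and between groups, with group as the between-participants factor and time as the covariate. Non-parametric substitutes are named for use if normality fails.
- **Error level** (same section): "Statistical significance will be accepted at α = 0.05". No adjustment or testing order is given.
- **Sample size** (same section): "Assuming a power of 80% and a two-sided 5% significance level, a total of 25 participants in each group would be required". The mean change of 21 points and SD of 6.6 are quoted for a 12-week intervention. The 15-point target is not tied to a visit.

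**The concern.** A primary outcome has to tell the analyst which comparison decides the trial. Here the definition gives several visits equal standing. One of them duplicates another and has no place in the visit schedule. The statistical section does not resolve this: it names a model for VISA-A but not which term or visit from that model decides, and it places visit-by-visit t-tests alongside without ranking them.

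Two things are at stake. First, if each listed visit may support a positive primary result at 0.05, the overall error rate is above the 5% used in the sample-size statement. Second, the choice of visit or contrast could be made after the data are seen, and nothing in the text would show that it had been. The planning figures also describe a 12-week change, so they do not speak to the outcome as defined across all visits.

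**Working it through.** **1. Count the visits.** VISA-A definition: 6 weeks, 12 weeks, 3 months, 6 months, 12 months. Table 3 after baseline: week 6, week 12, 6, 12 and 24 months. Both are measured from baseline, and Table 3 has nothing between week 12 and 6 months, so 12 weeks and 3 months are one assessment. That leaves k = 4 distinct primary visits.

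**2. The plan's own error figure.** One test at two-sided 0.05 gives 5%. This is the level in the sample-size statement, and it holds for a single named visit or a single overall contrast.

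**3. Bounds for four tests at 0.05, if any one may count as success.**
- Independent tests: 1 − (1 − 0.05)^4 = 1 − 0.8145 = 18.5%.
- Perfectly correlated tests: 5%.

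**4. Between the bounds.** The documents give no between-visit correlation, so it is assumed. A value near 0.5 is a reasonable low end for change scores. If raw scores have equal variance and equal correlation ρ, each change from baseline has variance 2(1 − ρ)σ² and two changes have covariance (1 − ρ)σ². Their correlation is therefore 0.5 whatever ρ is.

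Simulated probability that at least one of four standard normal statistics exceeds 1.96 in absolute value (1,000,000 draws), with a check by simulated t-tests at 25 per arm:

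| Correlation | Equal correlation | AR(1), adjacent visits | t-tests, 25 per arm, equal correlation |
|---|---|---|---|
| 0.5 | 15.5% | 16.7% | 15.7% |
| 0.7 | 13.1% | 14.3% | 13.0% |
| 0.8 | 11.4% | 12.6% | 11.8% |
| 0.9 | 9.4% | 10.4% | not run |

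**5. Does an ANCOVA run alongside add to this?** If its test is the overall group effect (the mean over the four visits), adding it as a fifth chance moves the equal-correlation rate from 15.6% to 15.8% at 0.5, from 13.0% to 13.1% at 0.7, and leaves it at 11.4% at 0.8 (2,000,000 draws; the starting values differ from the table only by simulation error). That is negligible. A group-by-time test could add more, but the article does not say which term it would test.

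**6. Rates under control.** One named contrast: 5%. Four co-primary visits with Bonferroni: 0.05/4 = 0.0125 per test.

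**7. Link to the sample size.** The quoted mean change and SD are 12-week figures, so week 12 is the only listed visit with planning data. Whether 25 per group follows from 15 points and an SD of 6.6 is a separate matter that does not affect this point.

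**The case against.** The best counter-argument is that the article does tie the primary outcome to one method. VISA-A change is the dependent variable of the repeated measures ANCOVA. The t-test sentence names no outcome and follows a sentence on descriptive statistics for all continuous variables, so it can be read as covering those variables generally. On that reading there are not four competing primary t-tests. This stands, and it narrows the point: what is missing is the deciding contrast within the model. It does not remove the point. The model is to test change both within and between groups, no group-by-time term or visit is singled out, and the t-tests are nowhere made subordinate.

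A reader might infer that the trial's false-positive rate is 11–15% as a matter of fact. The documents do not support that. They state no any-visit-wins rule, give no correlations, and do not call the t-tests primary.

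A reader might also count the absence of 24 months from the primary definition as an error. It is not one in itself: a visit can be scheduled without being primary. For that reason five-test rates are not used here.

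It may be said that a separate analysis plan could hold the multiplicity rule. It could, but a plan naming one visit would then conflict with the published definition, and the duplicated time point would remain.

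**Conclusion.** The point holds in a conditional form. Certain from the text: five time points are listed and four are distinct, the list does not match Table 3, and neither a deciding visit or contrast nor a multiplicity rule is given while every test is at 0.05.

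The size depends on how the result would be claimed. Under an any-visit rule with assumed equal correlations of 0.5 to 0.8, the false-positive rate is about 15% down to 11%; AR(1) correlation puts it about one point higher. With a single overall ANCOVA contrast as the sole primary test it is 5%. The text allows either claim, and that is the defect.

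**What to change.** By a dated amendment, made before any between-group comparison is looked at:

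1. Name one primary contrast at two-sided 5%. The natural choice is the between-group difference in VISA-A change from baseline to week 12, estimated from the repeated measures model. It falls at the end of the 12-week program and matches the period of the planning figures. A single pre-specified overall group contrast from the same model would control the error equally well and would stay closer to the multi-visit intent.
2. Delete '3 months' from the primary outcome definition, so that the visit list agrees with Table 3.
3. Make VISA-A at 6 weeks and at 6, 12 and 24 months secondary, and the per-visit t-tests likewise.
4. Bring the registry entry into line with the amended wording.

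No new data, visits or participants are needed. There are two costs. With week 12 as primary, late effects become secondary evidence. The primary outcome is also clarified mid-trial: 18 participants had been included by 9 November 2020 (Trial status). The amendment should therefore give its date and state that no between-group results had been seen.

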### Secondary outcome measures

#### Isokinetic plantar flexor strength

Reduced plantar flexor strength is a common feature in patients with Achilles tendinopathy [14–16, 39]. One prospective study to date established that plantar flexor torque below 50 Nm was a risk factor for developing AT [47]. Isokinetic testing is commonly used to measure plantar flexor peak torque [15, 16, 39].

Two separate protocols will be used for this test. In the first protocol, the participant will lie prone with full knee extension. In the second protocol, the participant will lie supine with 80° knee flexion. When the knee is flexed to greater than 60°, the force contribution of the biarticular gastrocnemius muscles to plantarflexion is reduced, and is thus representative of the force produced predominantly by soleus muscle [48]. If similar plantar flexor peak torque deficits exist between the two protocols, the identified deficits may thus be attributed to the soleus muscle [15] which will influence exercise prescription.

The testing will be performed on a isokinetic dynamometer (Cybex Norm, Computer Sports Medicine Inc.). In both protocols, the participant will have their foot strapped to a pedal with the centre of axis of rotation aligned with the medial malleolus and a correction for gravity applied. Beginning with their uninjured limb, participants will be asked to perform a warm-up involving 5 sub maximal concentric plantarflexion and dorsiflexion contractions increasing progressively from 60 to 100% of their self-perceived MVC for familiarisation. The participants will then be required to produce a maximal plantarflexion force over 5 repetitions for 2 sets with a 1 min rest between sets. Verbal encouragement will be provided to produce maximal effort through full range of motion for each repetition. In the second test, the participants will lie in supine position with the knee flexed to 80° in order to specifically test the peak torque of the soleus. The same familiarisation protocol, sets and repetitions as the previous test will apply. Both tests will use an angular velocity of 60° per second and operate through an ankle range of between 30° plantarflexion and 20° dorsiflexion. Data will be sampled at 100 and peak torque expressed as percentage of body mass (Nm/kg %) will be reported on both limbs. Between-limb asymmetries in peak torque will also reported and analysed.

#### Three-dimensional running gait analysis

Altered running biomechanics and muscle recruitment strategies have been highlighted in runners with AT [49–52]. Using a proprietary three-dimensional optical motion analysis system (Run 3D, Oxford, United Kingdom) the following kinematic and spatiotemporal variables will be measured: contact time, aerial time, stride length, stride frequency and joint angular displacements from initial contact to mid stance phase. Lower limb stiffness will be calculated using a validated equation based on the spring-mass model with running speed, contact time, body mass and leg length as inputs [53]. The participants will warm-up by running for between 2 and 5 min on the treadmill at a self-selected speed. Once they report that they are adequately warmed up they will be instructed to run at a speed that they feel they would be comfortable running at a steady pace for 30 min. Data will be captured for 30 s at a random interval over a 2 min period and the participants will not be informed about when the data capture begins. For the subsequent tests at week 6 and 12, the participants will be required to repeat the same speed for re-analysis.

#### Hop tests

Achilles tendon material properties contribute to stretch shortening cycle performance during hopping and jumping exercises [54, 55]. Reduced tendon mechanical properties, plantar flexor muscle rate of force development and deficits on a single forward hop test have previously been observed in patients with AT [23].

The hop tests will take place on two force platforms (AMTI, USA) to measure ground reaction force (GRF) data sampled at 1000 Hz. Ten infrared cameras (200 Hz; Bonita B10/Vero v2.2, Vicon, UK) will be used for three-dimensional motion capture. Reflective markers (14 mm diameter) placed on all relevant anatomical landmarks including the thorax, will be used in accordance with a modified Plug-in-gait model (Vicon, UK) [56], with centre of mass (COM) calculated from all segments. Motion and force data will be filtered using a fourth order zero-lag low pass Butterworth filter with a cut-off frequency of 15 Hz. The data will be exported to MATLAB 2015a (Mathworks, USA) for processing. Participants will perform 3 trials on each test, unshod and with hands placed on iliac crests.

##### Drop jump

Participants will perform both a double leg drop jump (DLDJ) and single leg drop jumps (SLDJ). The participants will complete a standardised warm-up which consists of 10 bodyweight squats, followed by 10 pogo hops in place and 3 familiarisation trials for both. A 30 cm box will be used for the DLDJ and a 20 cm box for the SLDJ. The participant who will be unshod with hands placed on iliac crests, will be required to drop off the box and rebound off the force plate as quickly as possible aiming for maximum jump height. They will be instructed to maintain knee and hip extension during flight phase and where there is visible evidence of knee flexion or a ‘tuck jump’, the trial will be deemed invalid and they will be asked to repeat until a competent trial is achieved. The ground contact phase will be defined by a GRF greater than 20 N and jump height will be calculated from centre of mass displacement using kinematic data. Reactive strength index (RSI), which is a measure of jump height divided by ground contact time, will be calculated for both the double and single leg drop jump.

##### Single leg hurdle hop

After completing the drop jump tests, participants will be asked to perform a single leg forward hurdle hop test (SLHH). The test requires that participants to perform a single leg forward hop over two 15 cm hurdles rebounding off the force platform in between, completing 3 trials on each leg. The participants will be instructed to rebound ‘as fast as possible’ and ‘as far as possible’, and to attempt to be fully stable on 1 leg upon landing. After each trial the participants will walk back slowly to begin the next trial taking approximately 10 s recovery time. Hop distance, rebound distance and contact time, as well as key biomechanical variables such as vertical, horizontal and leg ground reaction force, vertical, leg and joint stiffness, joint powers and moments, and joint angular displacements will be calculated using a custom MATLAB script (Mathworks, USA). Hop distance will be calculated as the distance from the initiation of the hop to the initial contact as the participants lands at the end of the hop and rebound distance from the force plate to the landing. Vertical stiffness (K_vert_) will be calculated at the point of maximum displacement of COM, as the ratio of change in vertical ground reaction force (GRF) to COM displacement:
$$ {\mathrm{K}}_{\mathrm{vert}}=\Delta \mathrm{Force}/\Delta \mathrm{CoM} $$

Leg stiffness will be calculated in the sagittal plane as the ratio of change in leg ground reaction force (F_leg_) to the change in leg length at the shortest leg length during stance phase as previously proposed [57]. Leg length is measured as the distance from the hip joint centre to the centre of pressure in the sagittal plane, while F_leg_ is calculated from the resultant GRF magnitude scaled to the leg angle using the trigonometry sine rule.
$$ {\mathrm{K}}_{\mathrm{leg}}=\Delta {\mathrm{F}}_{\mathrm{leg}}/\Delta \mathrm{Leg} $$

Joint stiffness (K_ankle_, K_knee_ and K_hip)_ at the ankle and knee, will be calculated in the sagittal plane as the ratio of change in joint moment to change in joint displacement:
$$ {\mathrm{K}}_{\mathrm{joint}}=\kern0.5em \Delta \kern0.5em \mathrm{moment}/\Delta \kern0.5em \mathrm{angle} $$

A pilot study has previously been carried out on 10 healthy participants prior to the commencement of the Achilles RCT study [58]. Good-to-excellent reliability (ICC > 0.75) was found for hop and rebound distance, contact time, knee and ankle joint stiffness, vertical and leg GRF, with moderate reliability (ICC 0.50–0.75) for reactive strength index, vertical and leg stiffness, ankle joint peak power, ankle and knee joint peak moments, and horizontal GRF. In a separate study using the same protocol, 3 trials were sufficient to obtain a stable measure of performance across key variables [59].

#### Training diary

In order to determine adherence and fidelity with the rehabilitation program and pain response to exercise, each patient will be required to complete a training diary logging their completed running and rehabilitation sessions as well as reporting any pain symptoms using a numerical pain rating scale (NPRS), that will be reviewed at week 6 and returned at week 12. Adherence is defined as the proportion of prescribed exercises completed while fidelity refers to whether the participant completed the prescribed exercises, sets, repetitions and target loads. Participants will be advised to take an extra recovery day between exercise sessions if pain was above 5/10 on the day after a session and to adjust their loads for the subsequent session.

#### Follow-up interviews

At 6, 12 and 24 months from baseline testing, patients will be required to complete a questionnaire [see Additional file 1: Appendix 1] to analyse their participation in their respective sport, document any re-injuries and to obtain patient satisfaction feedback on their respective rehabilitation program. These outcomes will be reported and compared between groups to determine if the rehabilitation program had any significant effect (Fig. 1).

**Fig. 1 Fig1:**
[figure not shown]
Study design flow chart

### Interventions

Each participant will be prescribed a graded rehabilitation exercise training program which they will perform at home or in a local gym. However, they will present themselves for one supervised session every 2–3 weeks by their respective group investigators to ensure compliance and appropriate progression. The patients following Silbernagel’s training program [see Table 1] will perform solely calf strength exercises with self-prescribed additional resistance and will progress their exercises based on a NPRS, where there is no greater than a 4/10 pain response during and in the 24 h following a training session. They will then progress to plyometric exercises as tolerated. The SSC6 group [see Table 2] will follow a multifactorial exercise program comprising of bilateral and unilateral kinetic chain strength, calf strength and plyometric training as well as running drills as early as they can tolerate them. The participants will enter at the highest level where they meet the minimum criteria. For the calf exercises, they will be encouraged to lift a certain percentage of bodyweight in additional resistance and increase weekly. A certain level of pain within tolerable limits will be accepted and participants will be encouraged to increase their resistance loading weekly so long as that pain doesn’t increase. Progression to Level 4 of the program will be based on achieving their prescribed exercise load targets and achieving a deficit of less than 10% between injured and uninjured limbs on the isokinetic strength tests. The reactive strength exercises will be performed at near maximal intensity for a set number of repetitions with good competency and within tolerable pain limits. The participants will progress to Level 5 when they can perform 10 single leg hops with a score of < 4/10 on the NPRS and progress from Level 5 when single leg RSI deficits are < 10%. Outcome measures will be monitored at the various timepoints and will be tracked according to reported NPRS ratings. In both groups, participants will be permitted to begin running in phase 2 when pain during daily activity is < 2/10 but will be advised on periodising their running and rehabilitation exercises throughout the week. Each participant will be provided with a training log in order to monitor training loads. Should an adverse event occur which results in re-injury or a new injury, the participant will be instructed to contact their respective investigator immediately so that they can be examined and their treatment will be adjusted, postponed or discontinued where appropriate. Upon completion of the training intervention, participants in both groups will be given a maintenance training program for 6 months. The design, prescription and reporting of the training intervention meets all of the 16-item checklist requirements in the Consensus on Exercise Reporting Template (CERT) [60] [Available in supplementary files].

See Tables 1 and 2 for an example of the exercise programs, and Table 4 for the points of difference between to two training interventions.

